#### Setting and participants

The study protocol was designed according to the Standards for Reporting Interventions in Clinical Trials Acupuncture (SRICTA) [17].

#### Sample size calculation

The sample size calculation is based on the two-sided chi-square test for difference with respect to the primary endpoint. There are few reports in the literature of clinical trialsof acupuncture treatment for depression insomnia. Based on our earlier randomized controlled pre-trial in Guangdong Provincial Hospital of TCM, we decided to adapt the reduction of the HAMD and PSQI scores as a baseline for the sample size calculation for our trial. We believe that the successful cure rate for depression insomnia is approximately 40% when adopting the conventional acupuncture formula and should be increased to 70% or more when using the optimized acupuncture formula. A sample size of 58 patients per group is necessary (as calculated using PEMS version3.1 software,with the predicted cure rates of 40% and 70%). The maximum dropout rate within the intervention is expected to be about 15%. Therefore, another 24 patients in total have to be randomized to obtain the required number of patients. The total number of patients needed to be randomized is therefore 140.

#### Recruitment of patients

The patients are referred by the doctors and acupuncturists from branch centers in Guangzhou, Huizhou, and Zhaoqing city. 70 patients are from Guangdong Provincial Hospital of TCM, 35 patients are from the second people’s hospital of Zhaoqing city, and another 35 patients are from the People’s Hospital of Huizhou city.

#### Randomizations and procedures for setting

The study procedures, risks, benefits, and data management are clarified in detail before the patients are asked to give their informed consent. To achieve comparable groups for known and unknown risk factors, a simple randomization is performed. Both groups have equal numbers of participants. The eligible participants are divided into two groups; the control group (indicated as 1 in the CRF) and the treatment group (indicated as 2 in the CRF). These groups will receive the acupuncture prescription as basic treatment but the treatment group will also be treated using the acupuncture points and techniques especially for insomnia. After inputting the estimated sample size into PEMS version 3.1, a sequence number, seed number, center number, and allocation result will be obtained. The allocation to the treatment or control group will then be performed using sealed consecutively numbered envelopes prepared by the trial team. Since this is a multicenter trial, after the patient is registered, the practitioners are informed, by telephone or other instant messenging, of the patient’s assignation to one of the two study formulas. This procedure ensures that the randomization is not influenced by the investigators taking part in this study. The practitioners participating in the study do not take part in the randomization process.

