### Data storage and statistical analysis of the trial outcomes

The data compilation form containing the variables of interest will be completed by the corresponding researcher at each center. Data will be documented in the paper CRF by researchers or evaluators and will be double-checked by quality inspectors. The supervisor will inspect the progress of the trial at regular intervals in each branch center. All the detailed original data (paper CRF) will be recorded timely, clearly, and completely. The case reports will be modified only by researchers who are documenting the data. The correct method of modification is tomark a line through the original record and write the revised data next to the original data,so that the change may be clearly visible. The modified data will be documented with data and the initials of the investigator. All the materials will be kept for 5 years after the completion of the study. At each center, the information obtained will be recorded on an electric database by EpiData software 3.1 at the same time, for subsequent statistical analysis.

Predictive Analytics Software (PASW, version18.0) is used for data analyses. Exploratory analysis will include the minimum, maximum, median, mean, and standard deviation. For measurement data, a normality test is necessary. Furthermore, baseline categorical data, demographic characteristics, such as sex and age category, and numerical data are analyzed with chi-squaretests and one-way analyses of variance (ANOVA). Student’s *t*tests are used tocompare different periods of measurement data. Wilcoxon matched-pairs signed-rank tests are used for ranked data. Independent Student’s *t*tests and 95% confidence intervals are used to detect differences between groups of the measurement data only if the normality test and analysis of variancetestsprove significant, otherwise rank-sum tests should be used, which are also used to detect differences between groups of ranked data. Linear mixed models (for continuous outcome variables) and generalized estimating equations (for categorical outcome variables) are used to examine changes over time and the severity of PSQI and HAMD. Both intention-to-treat and per-protocol analyses are used. Data from participants who do not violate the treatment protocols will be included in the per-protocol analysis. Missing data are dealt with using the ‘last value carried forward’ method.

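### Simple randomization does not guarantee the equal group numbers stated, and the unadjusted tests between groups give up precision that baseline PSQI and HAMD could supply

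*Protocol article*

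**What the plan says.** **Allocation.** The section on randomization in the protocol article states: "To achieve comparable groups for known and unknown risk factors, a simple randomization is performed. Both groups have equal numbers of participants". It adds that the software, given the estimated sample size, returns a sequence number, a seed, a centre number and the allocation. It mentions neither blocking nor stratification.

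**Centres.** Recruitment is fixed by centre: "70 patients are from Guangdong Provincial Hospital of TCM, 35 patients are from the second" hospital in Zhaoqing, and a further 35 come from Huizhou.

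**Analysis.** In the statistical analysis section, independent t tests with 95% confidence intervals "are used to detect differences between groups of the measurement data", with rank-sum tests as the alternative. Neither centre nor baseline score is named. The same section plans linear mixed models and generalized estimating equations for change over time in PSQI and HAMD, without giving their terms. PSQI and HAMD are the primary outcomes and are collected at baseline and at three later times.

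**Status.** The trial status section says the project ended in 2011, with results still to be published.

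**The concern.** Two adjoining sentences do not fit together. Simple randomization, in its usual sense, allocates each patient independently and leaves the group totals to chance, so equal totals need some form of restriction. A reader cannot tell which sentence describes what was done.

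The stated aim is comparability on known factors, and centre is a known factor: each centre has its own acupuncturists, and the optimized formula came from practice at the largest one. If allocation was not restricted by centre, the arms can differ by chance in how patients are spread over centres. The tests named for group differences would not correct for that.

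Those tests also make no use of the baseline score as a covariate. For scales measured before and after treatment this usually costs precision, and the data needed to avoid the loss are already collected.

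**Working it through.** **Inputs from the article.** 140 randomized; 1:1 ratio; centres of 70, 35 and 35; cure rates 40% and 70%; 58 per group; dropout about 15%. **Assumed, because not stated:** two-sided alpha 0.05, power 90%, and a baseline-outcome correlation ρ of 0.3 to 0.7.

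**1. The plan's own figure.** "The sample size calculation is based on the two-sided chi-square test for difference with respect to the primary endpoint", and "A sample size of 58 patients per group is necessary". With a mean rate of 0.55 and a difference of 0.30, the pooled-variance formula gives n = 2(1.960 + 1.282)² × 0.55 × 0.45 / 0.30² = 57.8, so 58 per group. Allowing for dropout, 116 / 0.85 = 136.5, so 137; the plan's 140 is close. The sample size is reproduced under the assumed alpha and power, and the rest of this point does not depend on it.

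**2. Group totals under simple randomization.** Let X be the number in one arm, X ~ Binomial(140, 0.5).
- P(X = 70) = C(140,70) / 2¹⁴⁰ = 0.067.
- P(arms differ by 10 or more) = 2·P(X ≤ 65) = 0.447.
- The 95% range for one arm is 58 to 82.

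**3. Balance within a centre of 35.**
- Simple randomization: 2·P(X ≤ 13), X ~ Binomial(35, 0.5), = 0.175 for a split of 22:13 or worse. For at least one of the two such centres: 1 − (1 − 0.175)² = 0.320.
- List forced to 70:70 overall but not by centre: 2·P(H ≤ 13), with H hypergeometric (35 drawn from 140, of whom 70 are in one arm), = 0.118.

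**4. Power cost of unequal arms** (40% against 70%, chi-square test).

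| Total | Equal arms | Average under simple randomization |
|---|---|---|
| 116 | 91.2% | 90.9% |
| 140 | 95.4% | 95.3% |

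Even a 58:82 split of 140 leaves 94.9%.

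**5. Precision from the baseline score.** Take equal variance σ² before and after treatment. Per patient, a final score has variance σ², a change score 2σ²(1 − ρ), and a baseline-adjusted score σ²(1 − ρ²). The adjusted variance is therefore 1 − ρ² of that for final scores, and (1 + ρ)/2 of that for change scores.

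| ρ (assumed) | Reduction against final scores | Reduction against change scores |
|---|---|---|
| 0.3 | 1 − 0.91 = 9% | 1 − 0.65 = 35% |
| 0.5 | 1 − 0.75 = 25% | 1 − 0.75 = 25% |
| 0.7 | 1 − 0.51 = 49% | 1 − 0.85 = 15% |

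At ρ = 0.5 the reduction is worth 1/0.75 = 1.33 times as many patients. The gain from adjusting for centre cannot be sized, because the article gives no between-centre variation.

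**The case against.** **On allocation.** A reader might infer that equal groups were impossible. The article does not support that. The list was generated for a fixed total, so it may have been forced to 70:70 with the word simple used loosely. The centre number in the output also leaves room for a list made per centre. In either case the 6.7% and 44.7% do not apply. This stands, and it is why the point is a conflict in wording that must be resolved, not proof of a faulty list. A list forced only overall would still leave centre balance to chance (step 3).

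**On the quotas.** A reader might also take the odd quotas of 35 as a contradiction. They are not one: equality is claimed for the groups as a whole, and two odd centres can add up to 70:70.

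**On harm.** Chance imbalance does not bias a randomized comparison in expectation, unequal arms cost almost no power, and no centre effect is shown. All of this stands.

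**On the analysis.** It would go too far to say that every planned analysis ignores baseline. The mixed models and estimating equations may use it, and their terms are ordinary content for the statistical analysis plan that the article mentions. That stands for those models. It does not cover the t and rank-sum tests, which the article itself names for detecting group differences and which carry no covariates.

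**On the figures.** The correlation is assumed, the gain depends on whether final or change scores would have been compared, and the factors in step 5 do not carry over to the binary cure rate on which the trial was sized. These limits are accepted.

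**Conclusion.** The point holds in a limited form. As written, the method and the equal-numbers statement do not agree: simple randomization gives 70:70 in 6.7% of cases and a difference of 10 or more in 44.7%. Control of balance by centre is not stated; a centre of 35 would split 22:13 or worse in 17.5% of cases, or about 12% if only the overall total was forced. The effect of unequal arms on power is negligible, about 0.1 to 0.2 percentage points on average.

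The consequence that matters is lost precision in the named between-group tests. For PSQI and HAMD as continuous scores, and for correlations of 0.3 to 0.7, baseline adjustment would remove 9% to 49% of the variance against final scores, or 35% down to 15% against change scores. The exact gain is unknown, but there is one at every assumed value. The improvement is worth making and can still be made before results are reported.

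**What to change.** 1. State the allocation method actually used: simple or restricted, and whether by centre. Correct the equal-numbers sentence to match, and report the number of patients in each arm by centre.
2. Make the between-arm comparison of PSQI and HAMD the linear mixed model already planned (or ANCOVA), with baseline score and centre as fixed effects, in place of the unadjusted t and rank-sum tests. If the analysis plan already specifies such a model, say that it is the comparison on which the conclusion rests.

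**Cost:** some wording, a count from existing records, and a model specification. No further patients or measurements are needed. The project has concluded, so a new randomization list or different centre quotas would serve no purpose and are not part of the fix.

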#### Blind method

All eligible participants take part in a double-blind study. The participants in both groups are blinded. The evaluation of participants and analysis of results will be performed by professionals blinded to the assignation of treatment options. Those blinded professionals are required to conduct the outcome assessments, collect medication diaries, and check any missing data. Except for the practitioners, all of those involved in the outcome assessment are blinded to participant allocation.

#### Study treatment

The patients taking part in the study will each receive 24 acupuncture sessions (twice per week), either conventional or optimized, as follows.

The treatment will be performed after sterilizing the skin on the acupuncture point areas and with patients lying face up. The temperature of the treatment room is not lower than 25°C.

1. Conventional acupuncture treatment

All the patients in intervention group 1, the control group, will receive the conventional acupuncture formula at the following points: LI-4 (He Gu), LIV-3(Tai Chong), EX-HN-3 (Yin Tang), and GV-20 (Bai Hui). The needles, size 0.35 × 25 mm,are produced by Suzhou Tianxie Acupuncture Instruments Co., Ltd. The needle are maintained in the acupuncture points for 30 minutes. During the treatment, after a De Qi sensation is produced, which is described as a numb, distended and aching sensation, patients are required to take six deep breaths and then have a rest, followed by another six deep breaths every minute until the needles are removed.

2. Optimized acupuncture treatment

The basic treatment formula is modified. On the basis of the normal acupuncture, LU-7 (Lie Que) and KID-6 (Zhao Hai) are added and needles remain in the body after patient feels the De Qi sensation. The embedded needles are then buried, for two groups of points (1) Bl-15 (Xin Shu), Bl-23 (Shen Shu), and Bl-19 (Dan Shu), N-HN-54 (An Mian); these two groups of points are used alternately. The granular type of embedded needle used has a needle tip of about 2 or 3 mm and is manufactured by Suzhou Medical Instrument Factory, China. The needle is inserted perpendicularly underneath the skin and is fixed with 3M medical proof fabric. Before the start of the next treatment, the embedded needles are removed.

To minimize treatment bias, all the acupuncturists who participate in this trial are acupuncturists of a general acupuncture department and each research center. They all gained medical licenses in China and were well trained according to the trial’s procedure under the guidance of senior acupuncturists.

### Common acupuncture adverse events or reactions and processing

#### Common acupuncture adverse events or reaction

1. Needle fainting during acupuncture treatment

For patients who are on their first visit or have a serious phobia about needles, a reassuring explanation is necessary. The patient’s complexion will be closely observed to check for any early symptoms of needle fainting, such as discomfort, dizziness, pale face, tiredness, sudden cold sweat, cold limbs, weak breathing, pale and green complexion, blue lips, low blood pressure, or obnubilation. If these symptoms occur, the needles should be removed as soon as possible. The patient is then kepthorizontal with feet slightly raised, and offered warm sugar water. If the symptoms are serious, DU-26 (Shui Gou), DU-25 (Su Liao), PC-6 (Nei Guan), and ST-36 (Zu San Li) points are selected as emergency points. If the symptoms persist, other professional hospital emergency measures may need to taken.

2. Convulsions

All acupuncturists must determine whether the participants have a history of convulsion.If a patient has a convulsion history during acupuncture treatment, close observation is needed. The practitioner will remove all the needles and take some emergency measures. If the disease is not immediately controlled or the convulsions persist, the participants must be transferred to the emergency center immediately.

3. Severe pains

Severe pains during and after treatment are usually caused by improper needle manipulation or strong stimulation. If the pain is of low intensity, a local compress is used to stop the pain; if the pain is heavier, moxibustion can be applied.

4. Needle sticking

If needle sticking occurs, the patients will be required to relax. If the stickingis caused by twisting the needle inone direction, the problem is solved by rotating the needle in the opposite direction. If the sticking is caused by the over-contraction of the muscle, the needles are removed and the local area of the acupuncture points is pressed, where the needle is stuck, or another needle is placed in the local area, to distract the patients’ attention. If the situation occurs because of a change in the patients’ position, it will be relieved when the patient resumes the correct position.

5. Local infections

If a strict aseptic operation is ignored, local infection occurs. Once the infection is diagnosed, proper treatment will be needed or drug therapy is suggested.

6. Subcutaneous hematoma

During the acupuncture treatment, swelling and bruising may occur when subcutaneous tiny vessels are broken. Ice and local pressure are used to stop the bleeding; at a later stage, a hot compress can be applied and herbs used, to promote blood circulation and remove the blood stasis.

#### Assessment of adverse events or reactions

If other adverse events or reactions occur during the study process, the investigator should analyze the situation, in particular:

1. The temporal relationship between the acupuncture and the adverse event, and whether there is aconnection.

2. Whether the adverse event or reaction is relieved on stopping the treatment.

3. Whether the adverse event or reaction occurs again, when repeating the acupuncture treatment, on the condition of ensuring the patient’s security and consent.

4. Whether the adverse events or reactions can be explained by the patient’s disease progress, a newly occurring disease, or other therapies self-administered by the patients.

#### Reportingadverse events orreactions

Any adverse events or reaction should be recorded in the appropriate form in the CRF. The adverse events will be reported to the principal investigator in Guangdong Provincial hospital and the result of the assessment will be recorded.

### Data collection and outcome assessment

The data required for evaluating the effectiveness of the treatment will be collected at baseline, at the start of the treatment, 1 month after the treatment has begun, 2 months after the treatment has begun, and at the end of the treatment. The data required for the blind method cognitive evaluation will be collected after the second acupuncture treatment and after the last treatment.

#### Primary outcomes

The PSQI, to ratesleep disorders, and HAMD, to rate depression, were applied as primary outcome measurements for effectiveness evaluation. The construction validity and reliability of the PSQI to measure changes in sleep qualityhave been proven in previous studies and this scale has been validated for use in China. The PSQI comprises 19 self-rated questions and 5 otherquestions, all grouped into seven component scores (subjective sleep quality, sleep latency, sleep duration, sleep efficiency, sleep disturbance, hypnotic medication use, daytime dysfunction), each weighted equally on a four-point scale, from 0 to 3. The seven component scores are then added to provide aPSQI score. A cutoff score of 5 has been recommended, with scores >5 indicating subjective insomnia [18]. Changes in levels of depression were measured on the Hamilton hetero-evaluation scale. There are three types of HAMD scale, with 17, 21, and 24 items. We used the 24-item HAMD scale. This scale is of proven discriminant validity, reliability, and sensitivity to change; moreover, it has been validated for use in China. According to the scoring standard, a normal score is less than 8; a score ≥8 and <20 indicates thatthe patient may have depression; a score of ≥20 and ≤35 indicates thatthe patient definitely has depression; anda scorehigher than 35 indicates that the patient has severe depression. In general, the higher the score, the more severe the depression [19].

#### Secondary outcomes

1. Combined medication record. Drugs such as antidepressants and hypnotics medication consumed during the trial (whether or not prescribed by the patient’s doctor) will be recorded and measured on a special scale. Antidepressants, analgesics, and NSAIDs consumed (whether or not prescribed by the patients doctor) atrandomization and at follow up will be documented. These will be measured on a four-point scale: 0=no medication; 1=less than the usual dose; 2=daily, at the usual dose,3=greater than the usual dose.

2. Blind method cognitive evaluation.

3. Baseline variables of patients such as age, sex, education level, profession, income level, weight (kg) and height (cm).

4. A record will be made of any side effects and possible adverse reactions arising from the treatment.

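### The listed safety outcome covers only effects attributed to treatment, which is narrower than the all-event recording rule and depends on a causality judgement whose blinding is not stated

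*Protocol article*

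**What the plan says.** Four places in the protocol article bear on this.

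- **Secondary outcomes, item 4** defines what is listed for safety: "A record will be made of any side effects and possible adverse reactions arising from the treatment".
- **Reporting adverse events or reactions** sets the recording rule, without a causal condition: "Any adverse events or reaction should be recorded in the appropriate form in the CRF". It continues: "The adverse events will be reported to the principal investigator in Guangdong Provincial hospital and the result of the assessment will be recorded".
- **Assessment of adverse events or reactions** assigns the causality analysis: "If other adverse events or reactions occur during the study process, the investigator should analyze the situation, in particular". Four considerations follow. They include "The temporal relationship between the acupuncture and the adverse event, and whether there is aconnection" and "Whether the adverse event or reaction is relieved on stopping the treatment". The other two are recurrence when acupuncture is repeated, and whether disease progress, a new disease or another therapy explains the event.
- **Blind method** lists the duties of the blinded staff: "Those blinded professionals are required to conduct the outcome assessments, collect medication diaries, and check any missing data". It then adds that everyone involved in outcome assessment, apart from the practitioners, is blinded to allocation.

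Study treatment describes embedded needles, fixed under medical fabric and kept in until the next session, for the optimized arm only. The statistical section describes no analysis of harms, whether of all events or of related events only.

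**The concern.** The recording rule takes in every event. The listed outcome takes in only those linked to treatment. To get from one to the other, someone must judge causality, and the article does not say whether that person knows the allocation.

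If that person does know it, the same event may be called related more readily in one arm than in the other. Embedded needles in one arm make this plausible: an event at a needle site tells whoever judges it which arm the patient is in. A table of related events would then partly reflect opinion on cause. It could show a difference that does not exist or hide one that does. A table of all recorded events does not depend on that step.

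**Working it through.** The document offers no safety figure to reproduce, so the check is mainly a comparison of the text.

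**Scope.** The recording rule covers any event or reaction. The listed outcome covers side effects and possible reactions that treatment brought about. The word for possibility lowers the threshold but does not remove the judgement. The second set is contained in the first, so the two sections differ in scope.

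**Who judges.** The assessment section names the investigator. It opens with events *other* than those already described, so on a natural reading it governs events outside the preceding list (needle fainting, convulsions, severe pain, needle sticking, local infection, subcutaneous hematoma). For the listed reactions the article names no one as judge of causality. In neither case does it state whether the person deciding is blinded.

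**Whether blinding reaches this step.** Causality is not among the named duties of the blinded staff. Against that, adverse reactions are a listed outcome, and all outcome assessors other than practitioners are said to be blinded. The text leaves the question open.

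**Illustration of direction, with assumed rates.** Only the sample size comes from the document: 140 randomized 1:1, so 140 / 2 = 70 per arm. The event rate and the attribution shares are assumptions. Let the rate of patients with an event be *p*, with one event per patient, and let *a* be the share attributed to treatment. The related-event rate is *p* × *a*.

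With *p* = 20% in both arms, each arm has 70 × 0.20 = 14 patients with an event.

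| Share attributed, arm A / arm B | Related, arm A | Related, arm B | Artificial gap |
|---|---|---|---|
| 50% / 50% | 14 × 0.50 = 7.0 | 14 × 0.50 = 7.0 | 0 points |
| 40% / 60% | 14 × 0.40 = 5.6 | 14 × 0.60 = 8.4 | 0.20 × 0.20 = 4 points |
| 30% / 70% | 14 × 0.30 = 4.2 | 14 × 0.70 = 9.8 | 0.20 × 0.40 = 8 points |
| 25% / 75% | 14 × 0.25 = 3.5 | 14 × 0.75 = 10.5 | 0.20 × 0.50 = 10 points |

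The all-cause comparison is 14 against 14 in every row.

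The bias can run either way:

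- No true difference, 80% attributed in the optimized arm and 50% in control: 0.20 × 0.80 = 16% against 0.20 × 0.50 = 10%, a false 6-point gap.
- A true 16% against 10%, with the shares reversed: 0.16 × 0.50 = 8% against 0.10 × 0.80 = 8%, so a real 6-point excess disappears.

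**The case against.** The strongest reply is that item 4 is a one-line statement about keeping a record. It sets no count, rate or exclusion, and its wording is inclusive. All events, together with the result of their assessment, go into the CRF in any case. How harms are tabulated is commonly left to a statistical analysis plan, and Study organization refers to one that is not shown.

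Much of this stands, and it rules out several stronger readings that a reader might infer:

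- *That unrelated events are left out of the report.* The article does not say so. Only the wording of the outcome is limited to treatment effects.
- *That the trial's comparison of harms rests on attribution.* No between-arm comparison of harms is stated, so there is none to call biased.
- *That causality is judged unblinded.* The article does not say the investigator is a practitioner, and its general statement on blinded assessors could cover this outcome.
- *That the investigator's causality analysis governs pain, infection or hematoma.* These are on the list of common reactions, and the assessment section addresses other events.
- *That worsening sleep or mood could be lost as disease progress.* PSQI and HAMD are the primary outcomes and are measured at 1 month, 2 months and the end of treatment, so worsening would appear there whatever its causal label.

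What the reply does not remove is the mismatch itself. This is not a complaint that a safety table is missing. The article states an outcome, and that outcome is narrower than the article's own recording rule. An analysis plan normally analyses the outcome the protocol defines.

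**Conclusion.** The concern holds as a mismatch of scope with a modest consequence. The listed safety outcome is worded by attribution, the recording rule is not, and the blinding of whoever makes the attribution is not stated. Attribution that differs by arm is a possibility the text leaves open; it is not shown.

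The size cannot be determined from the document. The gaps of 4 to 10 points, and the 6-point examples, rest wholly on an assumed event rate and assumed attribution shares. They should be read only as showing that a table of related events moves towards the arm where attribution is readier, while an all-cause table is unaffected by that step. An all-cause table would not correct for events being noticed or written down differently in the two arms.

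**What to change.** Reconcile Secondary outcomes with Reporting adverse events or reactions. Define the safety outcome as all adverse events recorded on the CRF form, of any cause, reported by randomized arm as the number of patients with at least one event and as event counts. Show events judged related only as a labelled subset, and state whether the person who judged them was blinded.

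The cost is a change of wording and one extra table, with more unrelated events listed. No new data are needed if the recording rule was followed. Trial status says the project concluded in 2011 with results still to be published, so the change concerns definition and reporting only. It alters nothing in how patients are managed.
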